#### Retrospective medical record audit

A retrospective audit of patient medical records will collect data relating to time-efficiency (e.g., occasions of service), patient safety and adverse outcomes (e.g., number of patient falls), AHP compliance to national stroke guidelines (e.g., assessment completed within 48 hours of admission), and utility of the TINSA (e.g., number of sections completed). The audit of each participant’s medical record will occur at least 2 weeks after patient discharge, to allow sufficient time for the paper medical records to be scanned onto the hospital’s electronic record system (Verdi).

#### 3-month follow up

To assess intermediate-term health outcomes, a follow-up phone call will be conducted by the Principal Investigator at 3-months after admission to the MHB ASU. The EQ-5D-3L will be used to assess self-reported quality of life, where overall health states will be compared [14]. To promote participant retention, the Principal Investigator will attempt to make contact on 3 occasions and leave voice messages. The Modified Rankin Scale (MRS) will be used to assess disability/dependence in activities of daily living after a stroke [15]. The standardised tools and a period of 3-months were selected for three reasons: 1) the timeframe is in line with the follow-up timeframes of 90–180 days used by the Australian Stroke Clinical Registry [16]; 2) standardised interviews using the Modified Rankin Scale are recommended at 3-months (90 days) following hospital discharge [17]; and 3) both measures are used by the National Stroke Foundation and the Australian Stroke Clinical Registry (AuSCR) for follow-up purposes in annual reporting [16]. Health-related questions will also be asked to assess the societal perspective of economic implications, focusing on falls in the community, increase in formal support services or informal supports, and readmissions to hospital.

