## Background

Allied health professionals (AHPs) are central to the provision of quality stroke services. The Australian stroke guidelines state that all people experiencing stroke should receive physiotherapist assessment within 24–48 hours of admission to hospital, and assessment by occupational therapists and speech pathologists within 48 hours of admission [1]. While each AHP has a clearly defined role, overlapping skills and knowledge result in some assessment tasks and questions being administered repeatedly by different clinicians [2–4]. At the Mater Hospital Brisbane (MHB) Acute Stroke Unit (ASU), the physiotherapist, occupational therapist, and speech pathologist assess patients presenting with stroke separately. However, these discipline-specific assessments overlap, for example the physiotherapist and occupational therapist both assess upper limb function and gather information on previous level of function and the home environment. Such duplication across allied health assessments is unnecessary, inefficient, and AHP time could be better utilised.

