**Fig. 2 Fig2:**
[figure not shown]
Recruitment timeline for patients and staff

Staff working on the MHB ASU will be provided with a Healthcare Provider Information and Consent Form before agreeing and completing the satisfaction and interprofessional trust surveys (see Additional file 3). The surveys will remain open for 5 business days and returned to a secure slot box or submitted online. Staff will be invited to participate in a focus group at the end of Phase 4. The ASU occupational therapists, physiotherapists, speech pathologists and social workers will be invited to complete a series of online staff confidence surveys before/after completing competency training and at monthly intervals during the implementation Phases 2 and 4. Patients and staff may decline to consent or withdraw their consent to participate at any point and for any reason without prejudice. Upon withdrawal no further data will be collected.

#### Baseline phases 1 and 3

For statistical purposes, the baseline data will be gleaned from Phases 1 and 3 where discipline-specific allied health stroke assessments are utilised within 48 hours for patients admitting to the MHB ASU (i.e., the existing physiotherapy, occupational therapy, and speech pathology stroke assessment).

#### Implementation phases 2 and 4

The novel TINSA (see Additional file 4) replaces discipline-specific allied health stroke assessments and will be utilised within 48 hours of admission to the MHB ASU in Phases 2 and 4. The novel TINSA has been developed in full collaboration with the health professionals on the MHB ASU, including occupational therapy, physiotherapy, speech pathology, social work, nursing staff, and the stroke clinical nurse consultant. The TINSA includes sections on social history, mood, previous level of function, home environment, communication, swallow, respiratory function, vision, cognition, upper limb function, lower limb function, and mobility. Due to the content and clinical skills required, the TINSA can be administered by trained physiotherapists or occupational therapists. The novel TINSA was approved and published in the hospital Policy and Procedure Library prior to use in the study.

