Patient outcomes at 3-months from hospital admission	• EQ-5D-3L as a measure of quality of life • Modified Rankin Scale (MRS) as a measure of disability • Health event questions pertaining to community falls, hospital readmissions, help from family/friends, formal support services.

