#### Economic evaluation

An economic evaluation will be performed alongside this study. Compared to usual discipline-specific assessment, we seek to determine the change in engagement of hospital resources when the novel TINSA is utilised with patients experiencing stroke. We expect the potential cost-saving to occur at the initial assessment phase of the hospital admission, while other costs incurred during or after the hospital admission will not be affected. The mean cost per patient will be calculated using a decision tree analysis with expected values calculated from observed patient scenarios. To do this, the analysis will take the approach of analysing outcomes in 3 different scopes from the perspective of the health sector (i.e., MHB where the study will take place). Scope 1 will evaluate the initial assessment phase of the hospital admission. Use of resources including AHP time and bed space will be evaluated using AHP assessment times and hospital coded data. Scope 2 will encompass the entire acute hospital admission (inclusive of Scope 1) with multiple measures available from patient medical records and administrative data collection such as occasions of service by AHPs, counts of adverse events (e.g., aspiration pneumonia), and hospital cost per diem (including equipment, consumables, maintenance, and overheads). Scope 3 will be the broadest view, evaluated 3-months after admission to the MHB ASU. In this scope, an extended healthcare perspective will be used, where relevant health costs and healthcare consequences for the patient post-discharge will be considered. For example, counts of adverse events (e.g., number of falls and unplanned readmissions to hospital), quality of life at 3 months measured using the EQ-5D-3L, and increased reliance on informal/formal supports will be compared between groups and (where possible) compared to national medians/means reported by the Australian Clinical Stroke Registry (AuSCR). A one-way sensitivity analysis will be performed to evaluate uncertainty in the cost estimates regarding the TINSA. For example, the costs of AHPs will be examined at the low and high ends of the clinical pay scale for the MHB ASU (e.g., from Health Practitioner Level 3.1 to Level 7.2) [19, 20]; the time of the TINSA assessment will be varied to represent two standard deviations above the mean (i.e., the scenario where costs calculated account for 95% of observations); and length of stay will be varied to represent two standard deviations above/below the mean to capture changes in hospital cost per diem (including equipment, consumables, maintenance, and overheads) for 95% of observations.

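### The 3-month Rankin and EQ-5D-3L comparisons between non-randomised phases should adjust for pre-stroke function, which both assessments record but the audit is not committed to extract; the increase in supports also needs a stated reference time

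*Protocol article*

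**What the plan says.** - **Design.** Study design (Protocol article) describes non-randomised comparative groups: Phase 1 against Phase 2 for mild stroke or TIA, Phase 3 against Phase 4 for moderate to severe stroke. Each baseline phase precedes its implementation phase.
- **Measurement.** Under 3-month follow up, "a follow-up phone call will be conducted by the Principal Investigator at 3-months after admission to the MHB ASU". On quality of life: "The EQ-5D-3L will be used to assess self-reported quality of life, where overall health states will be compared". The Modified Rankin Scale is taken at the same call. No pre-stroke value of either scale is mentioned.
- **Supports.** The same section speaks of an "increase in formal support services or informal supports". Economic evaluation, Scope 3, says "increased reliance on informal/formal supports will be compared between groups". Table 1 lists "Health event questions pertaining to community falls, hospital readmissions, help from family/friends, formal support services". None of the three gives the time from which an increase is counted.
- **What the assessments record.** Background says that in usual care the physiotherapist and occupational therapist both "gather information on previous level of function and the home environment". Implementation phases 2 and 4 says "The TINSA includes sections on social history, mood, previous level of function, home environment", among other items.
- **Audit.** Retrospective medical record audit names four domains (time-efficiency, safety, guideline compliance, TINSA utility), each with an example. Pre-stroke status is not among the domains or examples.
- **Adjustment.** Quantitative data analysis plans to look at the balance of potential confounders and to adjust if confounding becomes apparent. It names no covariate.
- **Identifiers.** Data management and monitoring has the participant identifier column deleted once data entry is complete and the study has closed.

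**The concern.** A patient who was dependent before the stroke can be expected to score worse on both scales three months later, whichever assessment was used. Nothing in a pre/post design with convenience sampling makes pre-stroke dependence similar between phases. If case mix differs, a comparison of 3-month levels mixes that difference with any consequence of the TINSA.

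These outcomes carry weight in the argument. The Discussion says that faster assessment must not come at the expense of patient outcomes, and Economic evaluation expects costs during and after admission to be unaffected. A case-mix difference could produce a false signal of harm or benefit, or mask a real one.

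The planned balance check cannot help with a variable that was not extracted. Once identifiers are deleted, the value can no longer be linked from the notes. This makes it a data-collection decision with a deadline, as well as an analysis detail.

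**Working it through.** **1. The plan's own figure.** Statistical power gives 26 per group for a 20-minute difference, SD 25, alpha 0.05 (taken as two-sided) and 80% power. Normal approximation: 2 × (1.960 + 0.842)² × (25/20)² = 24.5, so 25. The two-sample t-test gives 25.5, so 26. The figure reproduces. It concerns the primary outcome and is not in dispute. No sample size or power is stated for the 3-month outcomes, so 26 per group is used below only as a scale, before any loss to follow-up.

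**2. Shift from a pre-stroke imbalance.** Let Δ be the difference between phases in mean pre-stroke function (in SD) and r the within-phase correlation between pre-stroke function and the 3-month outcome. For a linear comparison of levels with no true effect, the expected difference is r × Δ. Both r and Δ are assumptions, because the article gives neither.

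| r | Δ = 0.3 SD | Δ = 0.5 SD |
|---|---|---|
| 0.3 | 0.09 | 0.15 |
| 0.5 | 0.15 | 0.25 |
| 0.7 | 0.21 | 0.35 |

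If the Rankin scale is analysed by logistic regression, the argument holds but these sizes do not carry over directly.

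**3. Scale of Δ.** With comparable case mix, the standard error of a baseline difference at 26 per group is √(2/26) = 0.28 SD. An imbalance beyond 0.3 SD would then arise by chance in 28% of comparisons, and beyond 0.5 SD in 7%. This chance part is already covered by the confidence interval and is not bias. The bias at issue is any systematic case-mix difference between periods, which comes on top and whose size is unknown.

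**4. Precision.** At 26 per group and 80% power, the detectable difference on unadjusted levels is 0.79 SD. A fixed covariate multiplies it by √(1 − r²), giving 0.76 (r = 0.3), 0.69 (r = 0.5) or 0.57 SD (r = 0.7). Here r is the correlation with the grade as coded from notes, so for the EQ-5D-3L the lower values may be the more relevant ones.

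**5. What adjustment leaves behind.** If the coded grade has reliability λ and its error is alike in both phases, the remaining shift is r × Δ × (1 − λ). It is smaller than r × Δ but not zero. If coding error differs between phases, a further term is added.

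**6. Supports: why the reference time matters.** Assume 30% v 40% of patients already had formal support and 15% of the others newly need it in both phases.

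- Level at 3 months: 0.30 + 0.70 × 0.15 = 40.5% v 0.40 + 0.60 × 0.15 = 49.0%, a difference of 8.5 points.
- New need since before admission, among all patients: 0.70 × 0.15 = 10.5% v 0.60 × 0.15 = 9.0%, a difference of 1.5 points.

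The same patients give very different contrasts depending on which quantity is recorded.

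**The case against.** The case against is substantial, and several parts of it stand.

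- **A reader might infer that the wording on supports contradicts Table 1, or that an increase cannot be obtained from one call.** The documents do not support this. The call can ask directly whether support has increased, and Table 1 names only the topic of the questions. The 8.5-point figure above would arise only if levels were compared, against what 3-month follow up and Economic evaluation both say. What remains is the unstated reference time.
- **A reader might infer that the audit excludes pre-stroke status.** The audit items are examples, and Table 1 is a complete list of outcomes, not covariates. The supportable statement is narrower: nothing in the article commits the study to extracting it.
- **The planned confounder check might cover it, and covariate lists commonly sit in the analysis plan.** It might, and failing to name covariates is not the point. The rule that is stated makes adjustment depend on an imbalance seen in small groups. Adjusting for one known prognostic variable fixed in advance is the better method.
- **Pre-admission supports may not be recorded in usual care.** This stands. Background mentions only previous function and home environment for usual care. Social history is named only for the TINSA.
- **The covariate is error-prone and its source differs between phases.** This stands too: separate discipline notes in Phases 1 and 3, the TINSA in Phases 2 and 4. Adjustment therefore cannot be said to remove the bias.
- **Levels are needed for the comparison with registry figures.** True, and reporting unadjusted levels alongside meets that need.

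**Conclusion.** The point holds as an inexpensive improvement to secondary and economic outcomes. The 3-month Rankin and EQ-5D-3L comparisons are open to confounding by pre-stroke dependence. The variable that would reduce it is recorded under both assessments, and the article does not secure it before identifiers are deleted. For illustration, a 0.3 SD imbalance shifts the difference by 0.09 to 0.21 SD for correlations of 0.3 to 0.7. All of these inputs are assumed.

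A reader might go further and infer that the phases do differ in pre-stroke dependence, or that such dependence largely determines the 3-month results. The documents show neither. The argument needs only some correlation and a design that does not secure balance. The primary outcome and its sample size are untouched.

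**What to change.** 1. Add pre-stroke function to the record audit in all four phases, coded by one fixed written rule (for example a pre-stroke Rankin grade), and complete the extraction before identifiers are deleted.
2. Include that value as a fixed covariate in the 3-month Rankin and EQ-5D-3L comparisons, whatever imbalance is observed. Keep reporting unadjusted levels for the registry comparison.
3. State pre-admission as the reference time for an increase in supports. Take the pre-admission value from the notes where it is recorded, and otherwise ask at the call about change since before admission.

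**Cost.** One or two audit items, a sentence in the analysis section and possibly one reworded question at a call that is already planned. No extra patient contact is needed. A note-derived grade carries coding error, and its source differs between phases. The report should therefore say that adjustment reduces the confounding and does not remove it.

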#### Staff and patient satisfaction surveys

The patient satisfaction survey asks participants to recall their experience of allied health assessment the previous day (see Additional file 5). The survey will be completed in written form if the patient remains in hospital, or via phone call if the patient has discharged from hospital. A paper-based staff satisfaction survey will ask MHB ASU staff to reflect on their experience of the TINSA (see Additional file 6). Both satisfaction surveys will utilise open-ended and multiple-choice questions.

#### Staff interprofessional trust survey

Staff interprofessional trust surveys will be completed during the first week of Phase 1 (i.e., the start of the study), the last week of Phase 3 (i.e., before the novel TINSA is used with the moderate to severe stroke population), and the last week of Phase 4 (i.e., the end of the study). Two surveys will be completed: 1) a validated team trust survey with relevance to healthcare [18]; and 2) a fit-for-purpose questions asking specifically about trust in transdisciplinary teams in healthcare settings (see Additional file 7).

#### Staff confidence surveys

Two online staff confidence surveys will be completed by occupational therapists and physiotherapists, one before and one after competency training. The surveys will ask about staff confidence to administer the TINSA. A series of online confidence surveys will be completed in monthly intervals during implementation Phases 2 and 4 by occupational therapists, physiotherapists, speech pathologists and social workers (see Additional file 8). The surveys ask about confidence to administer the TINSA, confidence to share clinical tasks, and confidence that referrals for other professionals are identified and appropriate.

#### Staff focus group

All staff working on the MHB ASU will be invited to join the staff focus group, to understand perspectives, professional impacts, benefits or drawbacks, value, challenges, utility, and sustainability of the TINSA. The staff focus group will be held at the end of Phase 4. The focus group will use open-ended and prompt questions and will be recorded and transcribed. A limit of 8 participants in the focus group is planned. If more staff are interested in being involved in a focus group, more than one group will be offered.

### Statistical analysis

#### Statistical power

The power calculation demonstrates the required participant number per phase to sufficiently power the study to find a minimal clinically important difference in the primary aim. The following time estimates represent the expert opinions of the AHPs working on the MHB ASU. The variation in time taken to complete discipline-specific occupational therapy, physiotherapy and speech pathology initial stroke assessment may range from 80 to 210 minutes total. The smallest clinically important improvement in time taken to allied health stroke assessment would be a decrease of 20 minutes in average total assessment time (i.e., enough time to complete another occasion of service or clinical task). Assuming a similar distribution of patients in each assessment group, a significance level of 0.05, 80% power and a standard deviation of 25 minutes, 26 patients per group will be required to detect a 20-minute difference in total assessment time.

#### Quantitative data analysis

For each participant group, two periods of time to measure standard discipline-specific allied health assessment and the TINSA assessment will be evaluated and compared. Patient characteristics, outcomes and quantitative survey responses will be summarised for each assessment group using frequency and percent for categorical variables, means and standard deviations for approximately normally distributed continuous variables, and medians and interquartile ranges for non-normally distributed continuous variables. Differences between assessment groups will be estimated using the general linear model for continuous outcomes and logistic regression for categorical outcomes. Balance of potential confounders between the assessment groups will be investigated and multivariable adjustment will be employed where there is an apparent confounding effect. Results will be presented as differences (continuous outcomes) and odds ratios (categorical outcomes) with 95% confidence intervals. All analyses will be performed using Stata 15.1 (Stata Corp, College Station, TX) and a *p*-value < 0.05 will be considered statistically significant throughout all inferential analysis.

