A transdisciplinary approach to allied health stroke assessment could streamline AHP services, which is pertinent given the increasing consumer demand for stroke care. In Australia, the number of new stroke diagnoses per year is predicted to grow from 27,000 in 2020 to exceed 50,000 by 2050 [5]. Transdisciplinary approaches are defined by their potential to build workforce capacity by blurring lines of traditional responsibilities and integrating aspects of care (such as assessment) to enable a single team member to deliver the occasion of service [6–9]. There is emerging evidence that demonstrates, when compared to usual care, hospital-based allied health transdisciplinary teams improve AHP time-efficiency, quality of care, and are cost-effective [3, 10, 11]. No negative or harmful outcomes were reported [3, 10, 11]. When pilot testing the allied health transdisciplinary assessment to be used in this study, the authors demonstrated a mean time saving of 103 minutes when the transdisciplinary assessment was used (42 minutes), compared to usual single-dicipline assessments (145 minutes) [12]. A time saving of 103 minutes could be clinically significant. For example, AHPs would have more time available to commence rehabilitation earlier in the patient episode of care, thereby aligning the service more closely with national stroke guidelines [1]. The pilot testing served as proof of concept for the study proposed in this paper. To the author’s knowledge, no other empirical studies have evaluated transdisciplinary approaches on ASUs. Due to the low volume of empirical evidence pertaining to transdisciplinary approaches on ASUs, alongside the potential for transdisciplinary approaches to streamline stroke services, empirical research is warranted in this field.

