### Study design

The clinical study of the TINSA is a pragmatic pre−/post four-phase mixed methods study with non-randomised comparative groups, a convergent parallel design, and longitudinal follow-up at 3-months after hospital admission. The main quantitative element of the study incorporates descriptive and cross-sectional analytic components and measures designed to evaluate and compare four periods of time during which existing and new transdisciplinary stroke assessments are evaluated (see Fig. 1). Only the allied health stroke assessment component of the patient admission to the MHB ASU will be evaluated, and subsequent allied health input will continue as per usual care. Phase 1 (baseline, usual care) and Phase 2 (implementation of TINSA) will recruit participants experiencing symptoms of mild stroke or Transient Ischaemic Attack (TIA) and evaluate usual assessment compared to the novel TINSA (respectively). Between Phases 1 and 2, a 1-month transition phase will take place to allow staff to become familiar with the novel TINSA, complete competency training, and practice the new clinical process. Phase 3 (baseline, usual care) and Phase 4 (implementation of TINSA) will recruit participants experiencing moderate to severe stroke symptoms to evaluate usual assessment compared to the novel TINSA (respectively). Phases 3 and 4 will occur in parallel with Phase 2 and be time-limited (3 months/phase) due to time constraints on the ASU. Due to the nature of the clinical processes and staffing on the MHB ASU, neither randomisation nor blinding are feasible.

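### The primary comparison of assessment time uses a linear model that by default assumes equal variances, which the protocol's own figures make unlikely; the confidence interval is misstated if phase sizes become unequal (low severity)

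*Protocol article*

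**What the plan says.** The Quantitative data analysis section names the model, "Differences between assessment groups will be estimated using the general linear model for continuous outcomes", and the form of reporting: "Results will be presented as differences (continuous outcomes) and odds ratios (categorical outcomes) with 95% confidence intervals". It mentions no allowance for unequal variance.

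The Statistical power section sizes the study for a 20-minute difference with a single SD and equal groups: "a significance level of 0.05, 80% power and a standard deviation of 25 minutes, 26 patients per group will be required to detect". The calculation is introduced by "Assuming a similar distribution of patients in each assessment group". It says that total usual-care time "may range from 80 to 210 minutes total". The Background gives the pilot means: "when the transdisciplinary assessment was used (42 minutes), compared to usual single-dicipline assessments (145 minutes". It gives no SDs.

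Three features of the design bear on this:
- Under the primary outcome heading, usual-care time covers the occupational therapist, physiotherapist and speech pathologist. Under the implementation phases, one trained physiotherapist or occupational therapist can give the TINSA.
- Patients are enrolled by convenience as they are admitted (Recruitment and consent), with no cap or ratio in the text.
- On timing, Study design says "Phases 3 and 4 will occur in parallel with Phase 2 and be time-limited (3 months/phase". The interprofessional trust survey section shows that Phase 3 ends before TINSA is used in moderate to severe stroke. Phases 3 and 4 are therefore sequential, and Phase 2 spans about 6 months. The length of Phase 1 is not in the text available here, and Fig. 1 is not shown.

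**The concern.** A linear model with the usual standard error estimates one variance from both groups together. If the groups differ in spread, this does little harm when they are equal in size. When they are not, the larger group dominates the pooled variance. If the larger group is the less variable one, the standard error is too small and the interval too narrow. If it is the more variable one, the interval is too wide.

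Both conditions are plausible here. A total over three assessments averaging 145 minutes should vary more than one assessment averaging 42. An SD of 25 on a mean of 42 puts the mean minus two SDs at 42 − 50 = −8 minutes, which no duration can reach. Nothing in the text holds the phases to equal size. What is at stake is whether the reported 95% interval for the primary outcome has its stated coverage. That should not depend on how many patients happen to arrive in each phase.

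**Working it through.** **The plan's own figure.** The target difference is "a decrease of 20 minutes in average total assessment time", with SD 25, two-sided 0.05 and 80% power.

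n = 2(1.960 + 0.842)² × 25² / 20² = 2 × 7.85 × 1.5625 = 24.5, so 25 per group by the normal approximation. With the noncentral t, power is 79.1% at 25 and 80.7% at 26. The stated 26 reproduces.

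**Inputs for the check**
- Usual-care SD: 25 min (Statistical power). As a cross-check, the expert range gives (210 − 80)/4 = 32.5.
- TINSA SD: *assumed*, as the documents give none. The low end takes the same coefficient of variation as usual care: 25 × 42/145 = 7.2. Values of 10 and 15 are also used.
- Phase sizes: 26:26 as planned. Other ratios are *assumed*, written as usual care:TINSA.

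**Formulas**
- Actual SE = √(s₁²/n₁ + s₂²/n₂)
- Pooled SE = √{[(n₁−1)s₁² + (n₂−1)s₂²]/(n₁+n₂−2) × (1/n₁ + 1/n₂)}

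**SEs with SD 25 and 7.24**
- 26:26: both are √[(625 + 52.4)/26] = 5.10, ratio 1.00.
- 26:52: actual √(625/26 + 52.4/52) = 5.00. Pooled √[(25×625 + 51×52.4)/76 × 0.0577] = 3.73. Ratio 0.75.
- 52:26: actual √(625/52 + 52.4/26) = 3.75. Pooled √[(51×625 + 25×52.4)/76 × 0.0577] = 5.02. Ratio 1.34.

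**Coverage of the pooled 95% interval** (normal data, 200,000 draws per cell, usual-care SD 25)

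| Usual care:TINSA | TINSA SD 7.2 | SD 10 | SD 15 |
|---|---|---|---|
| 26:26 | 94.5% | 94.8% | 94.9% |
| 26:39 | 89.6% | 90.6% | 92.5% |
| 26:52 | 85.3% | 87.2% | 90.5% |
| 26:78 | 78.2% | 81.7% | 87.6% |
| 39:26 | 97.8% | 97.5% | 96.8% |
| 52:26 | 99.0% | 98.7% | 97.7% |

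The Welch interval covers 94.9 to 95.1% throughout. With SD 32.5 v 9.4 (32.5 × 42/145), the pooled interval covers 85.3% at 26:52 and 78.2% at 26:78, so the result depends on the SD ratio and not on the value 25.

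**Does it change the answer against 20 minutes?** Take 26:52 and let the TINSA SD follow the TINSA mean.
- Saving 103 (TINSA mean 42, SD 7.2): about 96 to 110 pooled, about 93 to 113 with the actual SE. Both are far above 20.
- Saving 30 (mean 115, SD 25 × 115/145 = 19.8): coverage 93.1%. The intervals are 19.6 to 40.4 and 18.6 to 41.4, and neither clears 20.
- Saving 20 (mean 125, SD 25 × 125/145 = 21.6): coverage 93.8%.

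At 26:78 a rerun of the same simulation gave 91.9% for the 30-minute saving and 93.1% for the 20-minute saving. Near the threshold the shortfall is thus about 1 to 3 points.

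**The case against.** The strongest reply is that two inputs are not in the documents. No TINSA SD is reported, and unequal spread, though likely, is an inference. An SD of 25 on a mean of 42 is strained, but for a normal variable it puts only about 5% below zero. The size ratio is also unknown. The planned ratio is 1:1, where the interval is sound, and a long Phase 2 says nothing about its ratio to a Phase 1 of unstated length. Phases 3 and 4 have equal 3-month windows, so no systematic imbalance is implied there. All of this stands, and it makes the point conditional and centred on Phase 1 against Phase 2.

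A second reply is that robust standard errors are compatible with a general linear model, and an analysis plan not shown here may specify them. That stands too. The protocol does not rule the remedy out. It names a model whose default is doubtful on its own figures.

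A reader might go further and infer that the interval would be far too narrow and could falsely clear 20 minutes. The documents do not support this. The direction depends on which phase is larger. Severe under-coverage needs a small TINSA SD, and the ground for a small SD is the pilot mean of 42, that is, a saving of 103, where the lower limit is nowhere near 20. Combining that SD with a saving close to 20 would be inconsistent. Nor does the protocol say that the lower limit must exceed 20. It hypothesises a reduction of at least 20 minutes, powers for a 20-minute difference, and declares significance at p < 0.05.

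**Conclusion.** The point holds as a low-severity, conditional weakness. The stated model's default of one residual variance sits badly with the protocol's own figures for assessment time, and nothing in the text secures the equal sizes that would make this harmless. At 26:26 coverage is 94.5 to 95%. With SD 25 against an assumed 7.2 to 15, it falls to about 85 to 91% at 26:52 and 78 to 88% at 26:78, and rises to about 98 to 99% at 52:26. These figures rest on the assumed TINSA SDs, the assumed size ratios and normal data.

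The consequence is an inaccurate interval. A reversed conclusion against 20 minutes is unlikely. The argument from three assessments against one applies to total assessment time only and gives no ground for a claim about the other time outcomes.

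**What to change.** For total assessment time, state that the linear model will be fitted with heteroscedasticity-robust standard errors (in Stata, `regress` with `vce(hc3)`), or that a Welch comparison will be used when no adjustment is made. The robust option works with the planned multivariable adjustment and guards against error in both directions. It is best stated before the group SDs are seen.

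The cost is one model option and no extra data. If the variances prove equal, Welch loses practically nothing. In a two-group model HC3 uses s²/(n−1) in place of s²/n for each group, so at 26:26 the standard error is √(26/25) = 1.02 times as large, about 2% wider.
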